**Fig. 1 Fig1:**
[figure not shown]
Flowchart representing the research design with a convergent parallel mixed-method

As depicted below in Fig. 2, over the course of the study timeline each of the 21 participating centres will be defined as a cluster and randomly allocated to one of the seven groups. This allocation will follow a sequence similar to the observational and interventional periods. Randomisation of LTCF will be stratified by region; each group includes LTCF from the three participating regions.

The strategy used addresses issues related to incomplete design by minimizing the collection load to preserve good power by removing uninformative combinations of clusters and periods without too much alteration of the power [44]. A sequence includes: one or two pre-intervention observational periods of two months; one delivery intervention period of three months followed by an interventional consolidation period of three months; then a short-term observational period of two months; and 12 months after intervention a final observational period of two months, called autonomy.

The individual data collection is based on an open cohort: as the study progresses, some residents will leave the LTCF or die (on average 25% each year, but likely higher for subjects requiring palliative care), while others will be admitted to the LTCF or begin to require palliative care and will be included at a later date.

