### Outcome evaluation

#### Primary outcome measures

The primary outcome measures relate to the accurate identification of palliative care needs and early access to palliative care for residents in LTCF context. These will be assessed through a comparison of the pre- and post-intervention periods, with the main comparison focusing on the latest evaluation (autonomy). The following will be measured and compared:

1) Identification sensitivity: This main criterion is the proportion of residents identified by the LTCF team as in need of palliative care among those with “potential” palliative care needs identified proactively by a dedicated research nurse using “Gold Standards Framework Proactive Identification Guidance” [45] and the Palliative Care Indicator Tool (PICT) [46].

2) Access: The proportion of residents with effective access to palliative care delivery among those identified as in need of palliative care (with or without referral to the specialist palliative care service).

3) Optimal timing: We postulate that during the pre-intervention phase, the identification of residents’ palliative care needs is delayed and may not be systematically followed by the delivery of palliative care. Therefore, we will estimate the time gain by focusing on the interval between the time residents are identified as in need of palliative care and the time of their death (or discharge, withdraw from follow-up). An increase in this time can be interpreted as a shortening of the identification delay but also as an extension of the delivery period of palliative care and the identification of the need for palliative care, both of which would support the effectiveness of palliative care.

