#### Primary outcome analysis

The data analysis will be based on the comparison of data collected during pre-intervention versus post-intervention periods. The three primary criteria will be tested according to a hierarchical procedure: identification sensitivity, access, and optimal timing from a fixed sequence procedure; constructed using a pre-specified sequence of hypotheses; and endpoints ordered according to their importance [62]. All tests will be performed at the 0.05 level following the pre-specified order. Once one hypothesis is tested and the results indicate it is not significant, all subsequent tests will not be performed.

The statistical model will take into account the non-independence of the observations, as multiple evaluations may concern the same resident across time due to the use of open cohorts and several residents are included from the same LTCF. This hierarchy (three levels) leads to the use of generalized linear mixed models (GLMM) for repeated measures [63]. For dichotomous outcomes (i.e. the patient has been identified or not), we will use a Bernoulli distribution with a logistic link function, and for continuous outcomes a normal distribution with identity link function. The independent variables will be: the LTCF and the resident considered as random factors, the calendar time interval (common to all groups) considered as a fixed factor, and treatment mode for the cluster in the time interval (pre-intervention = control, post-intervention = experimental) considered as a fixed factor associated with the effect of the intervention. The chronological sequence of stepped wedge randomized trials means that the number of clusters exposed to the intervention being tested increases as the trial progresses [41].

The observation of an intervention effect may reflect the existence of an underlying secular trend that is independent of the intervention. Therefore, modelling the background secular trend is necessary to remove bias in estimating the effect attributed solely to the intervention. However, the saturated time parameterization (by J-1 indicators if there are J periods) may not be the most efficient approach if there are a large number of periods relative to the number of waves and clusters due to the reduced degree of freedom available for estimating the intervention effect. Thus, we will use a parsimonious specification with a minimum number of parameters, such as a polynomial specification to a fixed degree [64].

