To test the consistency of the hypothesis of a constant effect or conversely a time-varying intervention effect, we will develop a similar model with a random effects covariate representing the interaction of time by cluster. Finally, there may be variation across clusters in the magnitude of intervention effects that will be modelled by a cluster-period-specific random effect deviation [65] as this type of modelling also takes into account the incomplete structure of the stepped wedge design.

As additional exploratory analysis, the individual and institutional characteristics as well as the intensity of intervention will be used as explanatory or confounder factors as recommended in the literature and by expert opinion. In order to minimize the dimensionality of these factors, principal component analysis or a Lasso-type technique could be applied. The possible nonlinear effects of the continuous variables will be managed through fractional polynomials. The models’ performance will be assessed by the Akaike information criterion [66], and the stability of the estimates will be checked by resampling.

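### The random time-by-cluster term meant to examine whether the intervention effect is constant is largely blind to a loss of effect shared by all facilities

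*Protocol article*

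**What the plan says.** Four statements in the protocol article bear on this.

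- **Main model (Primary outcome analysis).** It has "the LTCF and the resident considered as random factors, the calendar time interval (common to all groups) considered as a fixed factor". Treatment enters once: "treatment mode for the cluster in the time interval (pre-intervention = control, post-intervention = experimental) considered as a fixed factor". Calendar time is to be kept parsimonious, "such as a polynomial specification to a fixed degree".
- **Constancy of effect (same section).** The question is a constant or "conversely a time-varying intervention effect, we will develop a similar model with a random effects covariate representing the interaction of time by cluster".
- **Differences in effect between facilities (next sentence).** "there may be variation across clusters in the magnitude of intervention effects that will be modelled by a cluster-period-specific random effect deviation".
- **Window of interest (Primary outcome measures).** Pre- and post-intervention periods are compared "with the main comparison focusing on the latest evaluation (autonomy").

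The schedule under Process evaluation design gives each sequence "one or two pre-intervention observational periods of two months", then "one delivery intervention period of three months followed by an interventional consolidation period of three months", then a short-term window, and an autonomy window 12 months after the intervention.

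**The concern.** The question posed is whether the intervention effect changes with time. The model offered adds a zero-mean random effect for facility by time. Its variance is zero when facilities share one time path and positive when they do not. Neither state says whether the average effect has changed since crossover.

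The next sentence has a similar mismatch. A cluster-period deviation, as worded, is not tied to treatment and could equally be present in usual-care windows. Variation in the size of the effect between facilities is a random coefficient on the treatment indicator.

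This matters because the main model gives the short-term and autonomy windows one common effect, while the main comparison is placed on autonomy and sustainability is a stated objective. The pooled effect represents autonomy only if the effect is the same in both windows. The model offered to examine that is poorly suited to showing a shared loss.

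**Working it through.** **1. What the term can see.** Let facility *c* have short-term outcome *Y(c,s)* and autonomy outcome *Y(c,a)*. With secular trend *f*, a loss of effect *D* common to all facilities and facility-by-window deviations *u*:

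*Y(c,a) − Y(c,s) = f(a) − f(s) − D + u(c,a) − u(c,s) + sampling error.*

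*D* moves the mean of this difference and leaves its between-facility variance unchanged. The added term estimates only the variance of *u*. *D* is largely taken up by the time polynomial and the single treatment term. Some misfit can leak into the variance, hence largely blind rather than wholly blind. This holds whether time means calendar time or time since crossover, because the term is random with mean zero.

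**2. The plan's own figures.** None is given for this check. The related figures reproduce. The arcsine effect size, 2·arcsin√p₂ − 2·arcsin√p₁, is 0.305 for 50 to 65% and 0.403 for 40 to 60% (stated 0.3 and 0.4). Also 21 × 25 × 2 = 1050 (stated 1000).

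**3. Simulation inputs.**

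- From the protocol: 21 facilities, 7 groups, one or two pre-windows, one short-term window, autonomy 12 months after the intervention, 40% rising to 60%, ICC between 0.02 and 0.1, 25 residents per facility.
- Assumed: steps of 2, 3 or 4 months between groups (Fig. 2 is not shown), which groups have two pre-windows, a linear or quadratic trend, cluster autocorrelation of 1 or 0.8, and no resident-level repeat correlation.
- Size: 72 facility-windows × 15 = 1080 observations, or 75 × 25 = 1875, both within the stated 1000 to 2000.
- Assumed variance test: likelihood ratio against a 50:50 chi-square mixture, cut-off 2.706.
- Monte Carlo error at 300 runs is at most √(0.25/300) = 2.9 points.

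**4. Effect falls uniformly from +20 points to 0, no facility drift.**

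| Setting | Variance test rejects | Fixed contrast rejects |
|---|---|---|
| 15 per window, 2-month steps | 3.7% | 52.0% |
| 15 per window, 3-month steps | 2.3% | 77.3% |
| 20 per window, ICC 0.05 | 6–10% | 62–83% |
| 25 per window, ICC 0.10, 2-month steps | 5% | 51% |
| 25 per window, ICC 0.05, 2-month steps | 4–5% | 64–70% |
| 25 per window, ICC 0.05, 3-month steps | 5% | 86–88% |
| 25 per window, ICC 0.05, 4-month steps | 7% | 97% |
| Logistic model, 25 per window, 3-month steps | 3% | 62% |

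Coding the term as a facility-specific time slope gives 2 to 6%. The highest rate for the variance test in any run without drift was 12% (30 points lost, ICC 0.02).

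**5. Constant effect of +20 points, variance test.**

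| Setting | Rejects |
|---|---|
| No facility-by-window fluctuation | 2–6% |
| Autocorrelation 0.8, ICC 0.02, 25 per window | 8% |
| Autocorrelation 0.8, ICC 0.05, 15 per window | 12–14% |
| Autocorrelation 0.8, ICC 0.05, 25 per window | 22–29% |
| Autocorrelation 0.8, ICC 0.10, 25 per window | 50–52% or 72%, in two separate simulations |

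**6. Separation of the two cases.** At ICC 0.05 and autocorrelation 0.8, constant versus fully lost gives 12% versus 16% (15 per window, 2-month steps) and 24–29% versus 29–36% (25 per window).

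**7. The fixed contrast under a constant effect.** It rejects 4 to 7% as a t-test in a linear model that keeps the facility-by-window effect, 5 to 10% as a likelihood-ratio test without that effect, and 11 to 13% in an uncorrected logistic fit (150 runs).

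**8. What anchors the contrast.** With equal steps of *d* months, and the 12 months counted from the end of consolidation, the first autonomy window opens 3 + 3 + 12 = 18 months after the first group's delivery starts. The last group leaves usual care at 6*d* = 12, 18 or 24 months, so control windows overlap autonomy only at *d* = 4. One group's autonomy window coincides with another's short-term window for 1, 3 or 4 pairs of groups at *d* = 2, 3 or 4. Elsewhere the contrast leans on the time polynomial.

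**The case against.** The strongest reply is that the variance test is a construction. The protocol says only that a similar model will be developed. It states no null, no likelihood-ratio test and no accept-or-reject rule, and its 0.05 level belongs to the ordered primary criteria. The model could be a supportive refit, outside that hierarchy. This stands as a limit on the rejection rates. It does not remove the mismatch, because a term with no treatment-by-time component cannot inform the question it is given, however it is judged. Restricting the deviation to post-intervention windows does not help: it rejects a full loss in 2–4% and, at autocorrelation 0.8, a constant effect in 13–16% (25 per window, ICC 0.05).

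Three stronger readings are tempting and unsupported.

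- **That a complete loss of effect would pass unnoticed, this being the only check.** The main comparison is placed on autonomy, and a pre-versus-autonomy comparison would show such a loss directly. Sustainability is also examined qualitatively.
- **That the term signals a time-varying effect whenever the effect is constant.** This needs facility-by-window fluctuation, for which the protocol gives no value.
- **That it has almost no power against any loss.** Only uniform loss was simulated. Loss that differs between facilities adds facility-by-time variance and would be partly detected.

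The sentence on effect variation is condensed and cites a source not at hand, which may tie the deviation to treatment. As written, it does not. The exact specification may be left to an analysis plan, but here a model is named and attached to a hypothesis, so this is not a missing detail.

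**Conclusion.** The point holds in limited form: the named term does not address the constancy question when the change is common to all facilities. Under an assumed 5% variance test and no facility drift, it rejects a uniform fall from +20 points to 0 in about 2 to 10% of trials, against about 50 to 97% for a fixed contrast. With an assumed autocorrelation of 0.8 it is positive under a constant effect in about 12 to 29% at ICC 0.05 and about 8% at ICC 0.02. Without fluctuation it stays near nominal.

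The mismatch follows from the text and the algebra alone. The sizes depend on assumed stagger, window size, autocorrelation and test, and separate simulations differ in size though not in direction. None of this shows that the hierarchical primary tests are invalid, and the random term remains useful for standard errors.

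**What to change.** In Primary outcome analysis:

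1. Examine constancy by replacing the single post-intervention indicator with short-term and autonomy fixed terms. Report their difference with a 95% CI, using a small-sample correction suited to 21 clusters.
2. Keep the time-by-cluster or cluster-period random effect in that model as a correlation term, and say that it is not read as evidence on constancy.
3. For variation in effect between facilities, use a cluster-level random coefficient on the treatment indicator.
4. State that a non-significant contrast does not establish a constant effect, and that the interval is what is interpreted.

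The cost is a change of wording, one extra fixed parameter in the constancy model and an additional fit, on data already to be collected. The downside is a possibly wide interval that leans on the time polynomial, because few control windows may overlap autonomy.

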In this study, the following research questions will be addressed: (1) To what extent was the early integrated palliative care model implemented as intended? (2) What were the factors that facilitated and hindered the implementation of early integrated palliative care in LTCF? (3) Does early integrated palliative care contribute to improved timely access to palliative care, quality of care, quality of life of residents, and quality of life at work for LTCF professionals?

Thus, the primary objective of this study is to assess the effectiveness of early integrated palliative care implementation in LTCF in terms of timely access to palliative care for older residents. This study also has two secondary objectives: (1) To identify factors that facilitate or hinder the implementation of early integrated palliative care and its sustainability in the LTCF context, and (2) To assess the effectiveness of early integrated palliative care in LTCF on (a) quality of palliative care services delivered (b) care pathway, (c) quality of life of residents and that of their family caregivers, and (d) quality of life at work for LTCF professionals.

We postulated that early integrated palliative care implementation should support person-centred care practices [29] and strengthen integrated care pathway for residents [27], and as a result improve quality of care and quality of life for LTCF residents and their relatives as well as quality of life at work for LTCF professionals. Therefore, the primary hypothesis addressed in this study is that implementing the early integrated palliative care should improve the timely identification of palliative care needs and access to palliative care for residents in LTCF with serious advanced chronic conditions requiring palliative care provision. The secondary hypotheses are: (1) Implementing early integrated palliative care should improve the quality of care delivered to LTCF residents; (2) Implementing early integrated palliative care should improve the quality of life of residents and their caregivers; and (3) Implementing early integrated palliative care should improve the quality of life at work for LTCF professionals.

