### Analysis

#### Quantitative analysis

The quantitative data will be analysed using R. Statistical analysis and will be performed after a blind review of data quality issues and a database “freeze.” Due to the sequence of interventions, the analysis cannot be carried out in a blinded fashion.

A patient flow chart will be set up according to the CONSORT extension recommendations for stepped wedge design [61]. Main analysis will be performed on all included residents following the intent-to-treat principle and according to the role assigned to each period (usual care in the pre-intervention period versus experimental care in the post-intervention period) regardless of whether palliative care was implemented.

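### The exploratory analysis lists delivered intervention intensity as a possible confounder, although intensity is part of the treatment; if entered raw beside the treatment term, it changes what that coefficient means and costs precision

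*Protocol article*

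**What the plan says.** All references are to the protocol article.

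- **Exploratory models** (Primary outcome analysis, last paragraph). The paragraph opens "As additional exploratory analysis, the individual and institutional characteristics" and gives one role to a mixed list: "individual and institutional characteristics as well as the intensity of intervention will be used as explanatory or confounder factors". To reduce the number of these factors, "principal component analysis or a Lasso-type technique could be applied".
- **Main model** (Primary outcome analysis). Facility and resident are random, calendar time is fixed, and the intervention effect is carried by "treatment mode for the cluster in the time interval (pre-intervention = control, post-intervention = experimental) considered as a fixed factor". Intensity is not in this model.
- **Analysis principle** (Quantitative analysis). Periods are analysed by their assigned role, "regardless of whether palliative care was implemented".
- **Order of periods** (Process evaluation design, text after Fig. 1). Each sequence starts with "one or two pre-intervention observational periods of two months; one delivery intervention period of three months", followed by consolidation and two later observation windows.
- **Research question 1** (Background). "To what extent was the early integrated palliative care model implemented as intended"

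**The concern.** Individual and institutional characteristics can exist before a facility crosses over, so adjusting for them is ordinary covariate adjustment. Intensity is different in kind. It takes a non-zero value only once the facility has crossed over, and how far each facility took up the intervention determines that value. A variable that is a component of the treatment cannot be a confounder of it.

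If intensity is nevertheless placed in the adjustment set with the binary treatment term kept, the treatment coefficient no longer compares intervention with usual care. It estimates what crossover does at zero delivered intensity, a point outside the exposed data unless some facility delivered nothing. A small or imprecise coefficient could then be reported as an intervention effect explained away by confounding, when the intervention had in fact worked in proportion to what was delivered. Passing intensity through PCA or Lasso together with case-mix variables would make this harder to notice. Intensity is also the natural quantitative measure for the trial's first research question, where it should be the exposure of interest and not a nuisance variable.

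**Working it through.** The article gives no figure on this point to reproduce. The check is an algebraic argument followed by an illustration.

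**1. Algebra.** Let X = 0 in pre-intervention windows and 1 in post-intervention windows, let d be the facility's delivered intensity, and D = d·X. Zero intensity in control windows is inferred from the order of periods; the article does not state how intensity is coded. The linear predictor is

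b_X·X + b_D·D = (b_X + b_D·m)·X + b_D·(D − m)·X,

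where m is mean intensity among post-intervention windows. This gives two results:
- with raw D, b_X is the effect at d = 0; with D centred among exposed windows, the treatment coefficient is the effect at mean intensity;
- fit and slope b_D are identical in both forms, so only the meaning and precision of the treatment coefficient change.

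**2. Inputs from the article (Sample size and power calculations; Process evaluation design).**
- 21 facilities in seven groups; one or two pre-intervention windows and two post-intervention windows.
- Effect from 40% to 60%, that is +20 points. The article's effect size for this is 0.4: 2·asin(√0.60) − 2·asin(√0.40) = 0.403, which agrees.
- About 1000 observations: 21 × 25 × 2 = 1050.

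**3. Assumed inputs (not in the article).**
- Intensity among exposed facilities: mean 1, coefficient of variation (CV) 0.2, 0.3 or 0.5.
- Share of the effect that runs through intensity: 0%, 50% or 100%.
- 13 residents per window. With one pre-intervention window in the first group and two in the others, there are 21 × 3 + 18 = 81 windows, and 81 × 13 = 1053 observations.
- Facility SD 0.11, an intra-cluster correlation of about 0.11²/(0.4 × 0.6) = 0.05, inside the article's 0.02 to 0.1.
- Groups two months apart; secular trend 0.2 points per month.

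Each scenario had 400 runs, fitted by linear probability regression with facility fixed effects and a linear time trend. This simplifies the planned logistic mixed model and has no resident-level correlation.

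**4. Results** (mean coefficient, mean SE in brackets, share of runs with |estimate/SE| > 1.96):

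| Effect through dose | CV | Treatment alone | Treatment, raw intensity added | Intensity coefficient | Treatment, centred intensity added |
|---|---|---|---|---|---|
| 0% | 0.2 | 0.198 (0.057), 91% | 0.193 (0.164), 24% | 0.005 | 0.198 (0.057), 91% |
| 0% | 0.3 | 0.203 (0.058), 94% | 0.210 (0.121), 43% | −0.007 | 0.203 (0.058), 94% |
| 0% | 0.5 | 0.200 (0.058), 94% | 0.198 (0.087), 61% | 0.002 | 0.200 (0.058), 94% |
| 50% | 0.2 | 0.204 (0.058), 95% | 0.093 (0.168), 8% | 0.110 | 0.204 (0.058), 94% |
| 50% | 0.3 | 0.198 (0.058), 89% | 0.103 (0.119), 15% | 0.096 | 0.198 (0.058), 89% |
| 50% | 0.5 | 0.201 (0.058), 92% | 0.102 (0.086), 24% | 0.098 | 0.201 (0.057), 93% |
| 100% | 0.2 | 0.201 (0.058), 94% | 0.010 (0.167), 4% | 0.191 | 0.201 (0.057), 94% |
| 100% | 0.3 | 0.197 (0.059), 91% | −0.007 (0.119), 6% | 0.204 | 0.197 (0.057), 92% |
| 100% | 0.5 | 0.200 (0.062), 90% | 0.001 (0.086), 8% | 0.197 | 0.200 (0.057), 94% |

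**5. Reading.** What leaves the treatment coefficient appears in the intensity coefficient: for 100% and CV 0.3, −0.007 + 0.204 × 1 = 0.197, the centred value. Even when dose carries none of the effect, the SE of the treatment coefficient rises by a factor of 0.087/0.058 = 1.5 (CV 0.5) to 0.164/0.057 = 2.9 (CV 0.2). The more uniform the delivery, the nearer X and D are to collinear and the greater the loss.

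**The case against.** The strongest reply is that the article does not commit to the faulty model. It says explanatory or confounder for a mixed list, and an ordinary reader may give intensity the explanatory role. That is legitimate dose-response work and serves the first research question. The text does not say that intensity enters uncentred or that the binary treatment term stays beside it, and PCA and Lasso are only optional. Coding details of this kind commonly belong to an analysis plan, which is not shown. The analysis is also expressly additional and exploratory.

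Most of this stands, and it limits the point. What remains is wording that the article itself fixes: intensity sits in one set with case-mix variables, the confounder role is open to the whole set, and so is the reduction step. That role is wrong for intensity under any coding.

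A reader might infer three stronger things that the document does not support:
- **The main result is compromised.** It is not. The main model has no intensity term, the analysis follows assigned periods whatever was delivered, and the hierarchical tests do not use intensity.
- **Adjusting for intensity removes the effect.** That happens only if intensity is entered raw beside the treatment term and carries all of the effect. With smaller shares the loss is partial or nil.
- **The dose-response information is spoiled.** It is not. With both terms fitted, the slope comes from variation among exposed windows and is the same with or without centring.

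**Conclusion.** The point holds as a minor correction to an exploratory analysis. Intensity is part of the treatment and should not be eligible as a confounder or for a joint PCA/Lasso set with case-mix variables. If it is entered raw beside the treatment indicator, the treatment coefficient becomes an effect at zero delivered intensity. In the illustration, with a true effect of 0.20, that coefficient was 0.193 to 0.210 when no effect runs through dose, 0.093 to 0.103 when half does, and −0.007 to 0.010 when all does. Precision fell in every scenario.

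These sizes rest on an assumed intensity distribution, assumed shares of the effect through dose and a simplified linear model, so they show a range and do not predict this trial's result. Two premises do not depend on the simulation: delivery follows the control windows, from which zero intensity there is inferred, and centring is only a reparameterisation.

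**What to change.** Amend the exploratory paragraph as follows:
- Reserve the confounder role, and any PCA or Lasso step, for individual and institutional characteristics measured before crossover.
- Use intensity only as a dose-response term. Either let it replace the binary treatment term (zero in control windows, which assumes no effect at zero dose), or keep the treatment term and add intensity centred among post-intervention windows.
- Label the dose-response result as non-randomised, because facilities are randomised to the timing of crossover and not to the intensity they deliver.
- Do not present a treatment coefficient adjusted for raw intensity as a confounder-adjusted intervention effect.

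This takes a sentence or two of text and no new data, and leaves the primary analysis as it is. The only downside is one fewer covariate in an exploratory model.
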